**Materials and methods and analysis:**

The aim of this trial protocol is to evaluate the efficacy of the localized PEERS training program on social competence, depressed mood in a Chinese young adult population with depression. The primary outcome will be a change in self-reported depressive symptoms from baseline to week 3 post-randomization to week 6 post-randomization measured using the Liebowitz social anxiety scale (LSAS). Secondary outcomes include the rate of decline in severe social anxiety, the Social Avoidance and Distress Scale (SAD), the Social Self-Efficacy Scale (PSSE), and the Hamilton Depression Scale (HAMD-17). Data for each assessment will be collected at baseline, week 3 of the trial, and week 6 of the trial.

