## Materials and methods and analysis

### Study design

This study protocol conforms to the Standard Protocol Items: Recommendations for Interventional Trials (SPIRIT) guidelines (see Additional file 1) and accords with the SPIRIT Figure (Figure 1). The proposed PEERS training for the trial is based on literature research and expert discussion and is an optimized update of the original PEERS training program. Participant engagement in the trial will be divided into two phases, a non-intervention phase before randomization and an intervention phase 6 weeks after randomization. This trial was designed to validate the efficacy of the localized PEERS training, and therefore the control group in this trial will not receive any interventions other than usual care. Participants will be randomized by ward to receive the intervention, and due to the specific nature of the intervention, blinding will not apply to the interventionists, and the study will remain blind to scale assessors and data entry only.

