### Assignment of intervention

Prior to the start of the intervention, different ward were randomly divided into intervention and control groups using a coin toss by an investigator not involved in the implementation of the intervention to prevent contamination, and eligible subjects were sought within the respective ward.

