### Primary outcome

Liebowitz social anxiety (LSAS) at week 3 and week 6 of the intervention will be assessed to measure social anxiety.

The LSAS scale was developed by Liebowitz in 1987 (47). It is commonly used to assess subjects’ social anxiety and is one of the most commonly used scales to provide a good picture of a subject’s social situation. The 24-item scale assesses fear in 11 social and 13 operational contexts. Scored on a four-point scale, for the fear subscale: 0 (none); 1 (mild), tolerable; 2 (moderate), distressing; 3 (severe), seriously interferes with daily life and work. For the avoidance subscale: 0 (never), 1 (occasionally), 2 (often), 3 (always). The final scores are added together, and the higher the total score, the more severe the social anxiety state. Mild anxiety is defined as a total score of less than 16, while severe anxiety is defined as a score of more than 60 (48). The Chinese version of the LSAS was tested for reliability and validity, and the Correlation between the items and the total score was good, the Cronbach’s α coefficient of each subscale was greater than 0.9, and the total scale score of the retest reliability was 0.779, the scale was generally satisfactory (49).

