### Statistical analysis

#### Statistical data collection

The HAMD-17 scale will be administered by a professional psychologist, while the remaining LSAS, SAD, and PSSE scales will be completed on the spot by the assessor who will carefully explain the purpose of the study and the method of completion to the study participants and gain the support and understanding of the patients before completing the questionnaire. The scale assessors will be selected from those who do not perform clinical interventions to reduce bias due to subjective factors. A paper version of the questionnaire is given to inpatients, and patients are followed up by phone or text messages after they are discharged from the hospital. When all the scales have been collected, the information is promptly reviewed and confirmed, and patients are asked to cooperate in correcting any problems found.

Data entry will be carried out by investigators who are not involved in the implementation of the intervention. After the data has been safely collected and entered, the data collected will be statistically analyzed with SPSS 25.0. *P* < 0.05 means the differences are statistically significant.

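### Blinding limited to assessors and data entry gives the patient-derived primary LSAS little protection, and the assessment procedure as written may weaken it further

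*Protocol article*

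**What the plan says.** All references are to the protocol article.

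- **Scope of blinding (Study design).** Those delivering the intervention are not blinded, and "the study will remain blind to scale assessors and data entry only".
- **Allocation (Study design; Assignment of intervention).** "Participants will be randomized by ward to receive the intervention". The second section adds that "different ward were randomly divided into intervention and control groups using a coin toss by an investigator not involved in the implementation of the intervention", with eligible patients then sought inside the allocated wards.
- **Primary outcome.** "Liebowitz social anxiety (LSAS) at week 3 and week 6 of the intervention will be assessed to measure social anxiety". The abstract describes the primary outcome as a "change in self-reported depressive symptoms" and names the LSAS as its instrument.
- **Collection (Statistical data collection).** A psychologist administers the HAMD-17. For the LSAS, SAD and PSSE, the sentence names the assessor as the one who completes them at the visit, and describes the assessor as the person "who will carefully explain the purpose of the study and the method of completion to the study participants" beforehand. The section then says that "A paper version of the questionnaire is given to inpatients", with telephone or text contact after discharge.
- **Assessor safeguard (Outcome measure; Statistical data collection).** Assessors are chosen from people who do not deliver the intervention.

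**The concern.** Blinding an assessor protects a score to the extent that the assessor's judgement produces it. LSAS ratings of fear and avoidance are the patient's own account, and the patient knows which arm he or she is in. The control arm receives usual care with no attention control, so an expectation of benefit can arise in one arm only. If the assessor also restates the purpose of the study just before the week 3 and week 6 questionnaires, the procedure may reinforce that expectation at the moment of measurement. Any resulting bias would most plausibly favour PEERS.

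A second question is whether the assessors are masked at all. Not delivering the course makes them independent of it. It does not keep the allocation from them.

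**Working it through.** The protocol gives no figure on this point, so the check is a comparison of its sections.

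1. **Are patients blinded?** Study design restricts blinding to assessors and data entry. Under Intervention group, one arm attends lessons over six weeks; under Study design, the other receives usual care only. Patients will therefore know whether they attend lessons. This follows from the design and is not stated outright.

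2. **Who produces the LSAS score?** The text supports two readings.
   - *The patient fills in the form.* The paper form for inpatients ("A paper version of the questionnaire is given to inpatients") points this way. The abstract's self-report wording does too, but weakly: it covers only the primary outcome and attaches to depressive symptoms, which the LSAS does not measure. On this reading, assessor blinding does not touch the score.
   - *The assessor fills in the form.* This is the literal wording under Statistical data collection. A blinded assessor would then limit interviewer influence on prompting and recording, but the answers still come from the unblinded patient.

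   On either reading the source of the primary score is unblinded. The same holds for the SAD and PSSE.

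3. **When is the purpose explained?** The explanation ("who will carefully explain the purpose of the study and the method of completion to the study participants") is placed before completion, with no visit named. The scales are given at baseline, week 3 and week 6. Participants already provides for the purpose to be explained to participants. A repeat at weeks 3 and 6 would add no information needed to complete the form, and the text does not exclude one.

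4. **What keeps the arm from the assessor?** The stated safeguard is non-delivery of the intervention. Ward determines arm, so an assessor who knows which wards run the course, or sees it running, knows the arm of every inpatient there. The person who tossed the coin is described in the same terms as the assessors, as not involved in delivery, so the text does not separate the two roles. The inference is weaker for contact by telephone or text after discharge.

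5. **How much is affected?** Of the four scales (LSAS, SAD, PSSE, HAMD-17), three rest on patients' own answers: 3 of 4, including the primary. A bias in LSAS points would need a rate of expectancy-driven response, and the document gives none.

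**The case against.** The strongest reply is that the protocol makes no false statement. It never claims patient blinding, and unblinded patient-derived outcomes are hard to avoid when a skills course is compared with usual care. That stands: the weakness is the limited reach of the stated blinding. A journal article may also leave masking procedures to the full protocol. That stands for operational detail, but the placing of the purpose explanation and the conflict over who completes the scales are in the article itself.

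A reader might infer four stronger points, none of which the document supports.

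- **That assessors are in fact unmasked.** Ward allocation makes this possible; nothing says that assessors know which wards received PEERS.
- **That trained patients are told before each questionnaire that their social anxiety should fall.** The text neither says that the explanation is repeated at weeks 3 and 6 nor gives its content. It could equally describe a first-contact introduction.
- **That the bias can be set against the pilot effect in LSAS points.** Any assumed share of shifted ratings would have no basis in the document.
- **That the HAMD-17 can serve as a masked check on a positive LSAS.** It measures depression, not social anxiety. In the pilot (Table 3) it fell by 19.25 − 10.75 = 8.50 with PEERS and 19.50 − 11.50 = 8.00 in control, a difference of 0.50. The LSAS fell by 55.50 − 41.75 = 13.75 and 52.25 − 51.50 = 0.75, a difference of 13.00. The two scales did not move together, so one cannot confirm or refute the other.

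**Conclusion.** The point holds in a limited form. The stated blinding gives the primary LSAS little protection because the answers come from patients who know their arm. The assessment procedure leaves open two avoidable weaknesses: a possible expectancy cue at weeks 3 and 6, and assessor masking that rests on independence alone. Who completes the LSAS, SAD and PSSE must also be reconciled.

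The conclusion assumes that patients know whether they attend lessons, which the design makes near certain. The expectancy cue depends on the purpose being explained again after baseline; the risk of unmasking depends on assessors working on the wards or otherwise knowing the allocation. The size of any bias is unknown. This is an inexpensive improvement worth making, and it does not invalidate the design.

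**What to change.** 1. **Statistical data collection, purpose.** Explain the purpose once, at consent, as Participants already provides. At weeks 3 and 6, use a fixed neutral instruction covering only how to complete the form.
2. **HAMD-17 rating.** Have it rated by study number, off the ward or by telephone, by someone with no ward information and no knowledge of the coin toss. Ask patients not to mention classes.
3. **Who completes the scales.** Reconcile the two statements on the LSAS, SAD and PSSE, and describe these scales as reports from unblinded patients. In Study design, word the blinding statement to match.

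The cost is a short script, minor logistics for off-ward or telephone rating, and a more modest blinding claim. The design and sample size do not change.

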**FIGURE 1 F1:**
[figure not shown]
Schedule of enrollment, intervention, and assessment (m = month, w = week).

### Participants

Trial participants were recruited from young adults with depression attending a specialist mental health hospital in Huzhou from July 2022 to January 2023. It is the largest specialist mental health hospital in the region, with psychological and psychiatric disorders diagnosis and treatment as its specialty, treating people with all types of psychosomatic disorders, with a wide range of influences and strong representation.

The purpose, procedures, possible risks, benefits, and other information about this trial will be explained in detail to participants. The trial participant schedule is specified in Figure 2.

**FIGURE 2 F2:**
[figure not shown]
Participant timeline.

### Inclusion criteria

① Aged 18–28°year (45).

② Willing and able to give informed consent.

③ The patient meets the diagnostic criteria for depression of the International Statistical Classification of Diseases and Related Health Problems 10th Revision (ICD-10) and gets HAMD-17 (≥ 18 points) and without other comorbid psychiatric disorders and two or more associate or chief physicians diagnosed with depression.

④ Patient has some degree of social impairment (LSAS ≥ 16 points).

⑤ Normal intelligence, without severe speech or emotional expression disorders.

⑥ Patients using SSRI antidepressants.

### Exclusion criteria

①Visual impairment, hearing impairment, or a serious physical illness that may affect the delivery of the intervention.②Substance abuse and dependent patients.③Have a serious neurological disease or mental disorder.④Patients suffering from post-schizophrenic depression.⑤Bipolar disorder, depression in bipolar disorder.

### Withdrawal criteria

① Patient-initiated withdrawal from the trial.

② Non-cooperation of the patient during the trial.

③ Those whose condition worsened during the study and were transferred to an enclosed ward.

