### Outcome measure

The measurement of each scale measure, the outcome indicators will all be carried out by investigators who are not involved in the implementation of the intervention.

A baseline survey will be conducted by the investigator after the study subjects are identified, and basic information will be collected on the subjects, including age, gender, marital status, mode of payment (self-pay, agricultural insurance, medical insurance, and others), type of depression (general depressive disorder, anxiety depressive disorder, and others), previous history, family history, duration of illness and medication use, etc.

Considering that the first onset of action of antidepressants is between 2 and 4°weeks (46), We, therefore, chose to collect the subjects’ depression scores at three-time points: baseline, week 3 of the intervention and week 6 of the intervention. The scales were selected based on clinical applicability and reliability to dynamically assess the efficacy of the localized PEERS training.

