#### Official experiment

This trial is a clinical intervention study, and the primary outcome indicator is the LSAS score. Compare sample size formulae based on means $n=\frac{2^{2}\,{\left(\mu_{\alpha }+\mu_{\beta }\right)}^{2}\,\sigma^{2}}{\delta^{2}}$. Take α = 0.05, β = 0.10. From the pre-test, we can calculate that σ2 = 243.04 and δ2 = 272.25, estimating a sample size of about 62 cases, and considering a 20% missed visit, 62 + 62*0.2 = 74, 74 patients are to be included in the formal trial, 37 in the intervention group and 37 in the control group.

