### Statistical methods

For baseline comparisons, age, LSAS scores, SAD scores, PSSE scores, and total HAMD-17 scores are measurement data for both two groups and will be statistically described using the mean ± S.D., with Paired Sample *T*-Test used to assess between-group balance. The general profile of the test subjects, including gender, education level, occupation, marital status, mode of payment for medical care, per capita household income, type of depression, duration of illness, type of medication, family history, and past history, are all categorical data that will be statistically described using frequencies and percentages, and chi-square tests to assess between-group balance.

The primary outcome indicators (LSAS scores at week 3 and week 6 post-intervention for two groups of patients) and secondary outcome indicators (SAD, PSSE, HAMD-17 scores at week 3 and week 6 post-intervention for two groups of patients) will be compared using Repeated Measures ANOVA to analyze the efficacy of PEERS training at different time periods. Considering the possible interaction between intervention and time, we choose Simple Effects to analyze the different effects of different time variances on PEERS training.

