The design of the experiment took into account the possibility of changes in the subject’s condition, and thus we set a 20% lost visit to ensure an adequate sample size. The intervention course is arranged in four interlocking sessions to refresh the knowledge taught and apply it to practice, while arranging for the coaches to take the lead and ensure the course is conducted properly, but more so to encourage the hands-on practice by the patients, using the class as an opportunity for patients to communicate and learn from each other, promoting their understanding of each other and helping each other to practice their social skills.

Before the formal trial began, a pre-experiment was conducted to examine both the motivation and cooperation of the study subjects. At the same time, the content of the sessions was improved to make the program more relevant to the actual needs of young people with depression, based on the subjects’ self-specific feelings and evaluations. The pre-experiment followed strictly to inclusion and exclusion criteria for the selection of subjects and was randomized to prevent cross-contamination between subjects. We found that all study participants cooperated positively with the study, were highly compliant and were able to successfully complete all training sessions without dangerous negative emotions or side effects, validating the reliability and safety of the training in this study. After the pre-experiment, social anxiety scores, social avoidance and distress mood decreased in the intervention group compared to the control group, while social self-efficacy scores increased relatively after the intervention, as detailed in Table 3.

**TABLE 3 T3:** The grading of the pre-experiment (n1 = n2 = 6; LASA, Liebowitz social anxiety scale; SAD, social avoidance and distress scale; PSSE, scale of perceived social self-efficacy; HAMD-17, Hamilton depression scale).

Entries	Before the trial		After the trial	
	Intervention group	Control group	Intervention group	Control group
LSAS	55.50 ± 21.20	52.25 ± 20.30	41.75 ± 17.21	51.50 ± 13.90
SAD	22.50 ± 3.64	22.25 ± 3.90	16.25 ± 5.31	22.00 ± 4.30
PSSE	52.2 ± 10.35	43.75 ± 4.66	54.50 ± 7.92	45.00 ± 7.45
HAMD-17	19.25 ± 1.75	19.50 ± 1.19	10.75 ± 1.48	11.50 ± 2.06

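### Withdrawal for non-cooperation or for worsening with transfer, followed by a Repeated Measures ANOVA, would in practice make the primary LSAS comparison one among completers

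*Protocol article*

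**What the plan says.** Withdrawal criteria (protocol article) has three items. The first is the patient's own decision to leave the trial. The second is "Non-cooperation of the patient during the trial". The third is "Those whose condition worsened during the study and were transferred to an enclosed ward". The section does not say whether items 2 and 3 end the training, the assessments or both.

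Outcome measure sets the scores at "baseline, week 3 of the intervention and week 6 of the intervention". Statistical methods states that the primary LSAS scores and the secondary scales "will be compared using Repeated Measures ANOVA to analyze the efficacy of PEERS training at different time periods", and Statistical data collection adds that "the data collected will be statistically analyzed with SPSS 25.0". That section describes telephone or text follow-up only for patients who have been discharged.

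The Discussion says that possible changes in a patient's condition were considered, and gives the response: "we set a 20% lost visit to ensure an adequate sample size". Official experiment carries this out by raising 62 patients to 74, 37 per arm.

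**The concern.** Items 2 and 3 act after allocation. One depends on clinical course and the other on cooperation, and either may be affected by the arm the patient is in. If assessment stops at that point, the week-6 score is never obtained. In its standard SPSS form, Repeated Measures ANOVA then leaves the patient out altogether, including a week-3 score already collected. This holds whether or not baseline is entered as a time point, because week 6 is missing either way.

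The comparison would then no longer be of the groups as allocated. At stake is bias in the primary LSAS result, which more patients cannot cure. A later analysis plan could change the model or add imputation, but it could not recover scores that nobody collected. That is why the point belongs in the protocol.

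**Working it through.** **Inputs from the protocol.** Official experiment gives "Take α = 0.05, β = 0.10" and "σ2 = 243.04 and δ2 = 272.25", so SD = √243.04 = 15.59 and δ = √272.25 = 16.5. The allowance for loss is 20%, and the planned total is 74.

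**The plan's own figure.** The formula is n = 4(z_α + z_β)²σ²/δ². With one-sided α = 0.05 and power 0.90 it gives 30.58, rounded up to 31. Read as per arm, that is 62 in total, and 62 × 1.2 = 74.4, about 74. The stated 62 and 74 are reproduced on this reading.

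**How many patients are affected.** Expected loss is 74 × 0.20 = 14.8, about 15 patients. Those left are 74 × 0.80 = 59.2, about 59. The 20% covers all causes of loss; the protocol does not split it by reason or by arm.

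**Is this a power problem?** No. At δ = 16.5 and SD 15.59, treating patients as independent, two-sided power is 0.995 with 37 per arm and 0.981 with 29 per arm. What the larger sample protects is precision, and precision is not what is threatened.

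**Size of the bias.** Let p be the share lost in an arm and g the amount by which lost patients would have scored worse on LSAS than retained ones. The mean of all patients in an arm is the retained mean + p × g, so the retained mean is too low by p × g. The error in the control-minus-PEERS difference is therefore

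bias = (p_PEERS − p_control) × g.

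The documents give neither the p's by arm nor g. All values below are assumptions, with g = 10 to 20 points.

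| Lost, PEERS | Lost, control | Bias in LSAS points | Share of 16.5 |
|---|---|---|---|
| 20% | 20% | 0 | 0% |
| 20% | 5% | 0.15 × 10 to 20 = +1.5 to +3.0 | 9% to 18% |
| 10% | 20% | −0.10 × 10 to 20 = −1.0 to −2.0 | −6% to −12% |

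A positive sign overstates the benefit of PEERS; a negative sign understates it.

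**Cross-check with a different model.** Assume no true effect, SD 15.59, and withdrawal of the patients worst on a latent clinical course correlated 0.3 to 0.8 with LSAS. Losing 30% in one arm and 10% in the other creates a false difference of 1.4 to 3.8 points, 9% to 23% of 16.5. Losing 20% and 10% gives 0.7 to 1.9 points. Equal loss gives 0. Under this model the arm that loses more patients looks better.

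**The case against.** The strongest reply is that case deletion is nowhere written. The protocol names a method and a software version; it names no procedure, does not restrict the analysis to completers and does not exclude imputation. An analysis plan that is not shown may settle this. That is fair, and a reader should not infer that the protocol orders partial data to be discarded. What stands is that the named method in its standard form has this effect, and that no analysis plan can supply scores that were not collected.

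Second, only item 1 speaks of leaving the trial; items 2 and 3 do not say that assessment stops. This is true, but all three stand under one withdrawal heading, and follow-up is described only for discharged patients.

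Third, item 3 requires worsening and transfer together. A reader might infer that everyone who worsens, or the poorest LSAS responders, are removed. The text does not support that. The condition that worsens is presumably the depressive illness, and a patient whose LSAS rises without transfer stays in.

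Fourth, unequal loss is an inference. Only the PEERS arm has lessons and homework to refuse, but both arms complete scales and receive medication and psychotherapy. In the pilot all 12 participants are reported to have cooperated. Twelve patients cannot settle the matter, but they offer no evidence of imbalance.

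Fifth, safety is among the stated objectives, so a reader might infer that transfers for worsening disappear from the record. Nothing says that they will go uncounted; the text shown simply does not commit to reporting them by arm.

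**Conclusion.** The point holds as a flaw in how the withdrawal criteria and the primary analysis fit together. Followed as written, with the ANOVA in its standard form, the plan would compare completers selected partly on clinical course and cooperation. About 15 of 74 patients are expected to be lost, and the plan's stated answer, a larger sample, does not address bias.

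The bias cannot be sized or signed from the documents. It is about zero if loss and its mechanism are the same in both arms. The figure of 1.5 to 3.0 points rests wholly on assumed losses of 20% and 5% and an assumed gap of 10 to 20 points; reversing the imbalance reverses the sign. It would therefore be wrong to conclude that the trial will exaggerate the effect of PEERS. The supported conclusion is that the design leaves room for a bias in either direction that could largely be prevented by continuing to collect the scores.

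**What to change.** Leave the clinical decisions on transfer and on stopping training as they are, and change only data collection and analysis:

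1. State in Withdrawal criteria that items 2 and 3 do not end data collection.
2. Collect the week-3 and week-6 scales from these patients unless consent is withdrawn. Extend to transferred patients the follow-up that is now described only for discharged ones.
3. Replace the Repeated Measures ANOVA with a mixed model on all enrolled patients, by allocated ward, using every available visit.
4. Report transfers for worsening, and withdrawals with reasons, by arm.

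The cost is amended wording, a different model and a few extra scale administrations, some of them on the enclosed ward, where arrangements would be new. Some scores will still be missing. Step 2 is the essential one, because a mixed model alone does not cure loss that depends on unobserved outcomes.
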